# Impact of progesterone-free luteal phase support following natural cycle frozen embryo transfer: Study protocol for a multicenter, non-inferiority, randomized controlled trial

**DOI:** 10.3389/fmed.2022.1014946

**Published:** 2022-11-15

**Keywords:** luteal phase support (LPS), natural cycle, frozen embryo transfer (FET), spontaneous ovulation, assisted reproductive technology (ART)

## Abstract

**Introduction:**

Nowadays, frozen-thawed embryo transfer (FET) has become one of the standard treatments for infertility in the field of assisted reproductive technology (ART). Natural cycle FET (NC-FET) has many advantages, such as simplicity and economics, no effect on patients’ menstrual cycles, estrogen and progesterone levels, as well as no interference in endometrial growth and transformation, which is aligned with the natural physiological state of embryo implantation. Nonetheless, there is a controversy regarding the need for luteal phase support (LPS) during NC-FET cycles. The purpose of this study is to assess whether LPS was not inferior to non-LPS in terms of OPR in NC-FET cycles.

**Methods and analysis:**

This study including 1,010 ovulatory women undergoing *in vitro* fertilization (IVF)/intracytoplasmic sperm injection (ICSI) cycles with an elective freeze-all strategy followed by NC-FET will be performed at four university-affiliated reproductive centers. Participants will be randomly assigned in a 1:1 ratio to receive LPS treatment or not. This study is designed as an open-label, non-inferiority, randomized controlled trial (RCT), and the primary statistical strategies were intention-to-treat (ITT) and per-protocol (PP) analysis.

**Discussion:**

There may not have been any significant difference in the chance of a live birth after FET if no progesterone was supplemental during the luteal phase. However, due to the limited number of previous studies, which are mainly retrospective, evidence is still limited. Thus, by conducting this multicenter RCT, we intend to evaluate whether LPS is necessary in NC-FET.

**Ethics and dissemination:**

A Reproductive Ethics Committee of the Affiliated Hospital of Shandong University of Traditional Chinese Medicine (SDUTCM) has approved this study. This study will handle the data as required by general data protection regulations. Participants will sign a written informed consent regarding participation in the study and storage of blood samples in a biobank for future research. This study will be monitored by study personnel trained in Good Clinical Practice who are not involved in the study. The results of this study will be disseminated through publication in international peer-reviewed scientific journals.

**Clinical trial registration:**

[https://www.chictr.org.cn/], identifier [ChiCTR2200057498].

## Highlights

-The first clinical trial to demonstrate that NC-FET without LPS can be non-inferior to NC-FET with LPS, minimizing the pain and need for medication.-The purpose of this study is to provide more evidence-based support through a multicenter, non-inferiority, randomized controlled trial.-Physicians and participants could not be blinded to treatment allocation.

## Introduction

In recent years, with the significant improvement of ovarian stimulation regimens and embryo cryopreservation and thawing techniques, the frozen-thawed embryo transfer (FET) procedure has gained more popularity in assisted reproductive technology (ART) than fresh embryo transfer (1). Additionally, it has been shown that FET is effective in reducing the incidence of ovarian hyperstimulation syndrome (OHSS), preserving remaining embryos, and increasing the cumulative live birth rate (LBR) (2, 3). In general, NC-FET is indicated for patients who experience regular ovulation (4, 5). The NC-FET is cost-effective, does not affect the menstrual cycle, does not interfere with estrogen and progesterone (P_4_) levels, or endometrial growth and transformation, and conforms to the natural physiological state of embryo implantation, despite the disadvantages of repeated monitoring and high cancelation rates (6). Furthermore, a recent large retrospective study involving 14,421 cycles demonstrated a lower early pregnancy loss rate with NC-FET, while the LBR was higher.

In NC-FET cycles, the necessity of luteal phase support (LPS) is still controversial. An investigation of 84 UK IVF clinics revealed that, in natural FET cycles, 31% administer LPS always, while 44% administer it sometimes (7). In another online survey of 179 IVF clinics around the world (representing an estimated 39 thousand FET cycles annually), it was found that more than half (57%) of clinics are using LPS in natural FET cycles, and 49% of clinics are using P_4_ exclusively (8). Despite common use, LPS is not universally used in natural FET cycles, as both surveys underscore. In 2013, a RCT with small sample size (*n* = 102) conducted by Eftekhar et al. comparing NC-FET with no LPS, LPS did not result in higher clinical pregnancy and implantation rates or lower miscarriage rates (9). Coincidentally, Waldman et al. reported similar results in their retrospective study (10). Nevertheless, several recent studies showed that patients undergoing LPS with vaginal P_4_ in NC-FET had higher LBR and lower miscarriage rates (11–13). In addition to LPS with P_4_, patients who received LPS by intramuscular human chorionic gonadotropin (hCG) had a higher ongoing pregnancy rate (OPR) in NC-FET, whereas the RCT results of Lee et al. indicated that this LPS protocol did not exert a similar effect on the OPR (14, 15). Recent meta-analyses indicated a positive impact of P_4_ supplementation after FET in natural cycles (16–18), but further large RCTs are required to confirm these findings.

Therefore, it is still unclear whether or not we should perform LPS in NC-FET. Additionally, previous studies still have limitations such as single center, small sample size, large population heterogeneity, different types, routes and times of P_4_ administration, and inconsistent study endpoint settings. Thus, to determine whether LPS affects reproductive outcomes in NC-FETs, we conducted this well-designed RCT.

## Methods and analysis

### Study design

The study is designed as an open-label, non-inferiority RCT, including reproductive centers of four tertiary care hospitals in mainland China. The flow chart and study process schedule are shown in Figure 1 and Table 1.

**FIGURE 1 F1:**
[figure not shown]
Study flow chart.

**TABLE 1 T1:** Overview of study visits.

	Baseline * (2–4 days at menstruation)	Late follicular phase (8–12 days of menses) –ovulation day	D3 of embryo transfer (ovulation day + 4 days)	Blastocyst transfer (ovulation day + 6 days)	Day of pregnancy test (ET day + 14 days)	Pregnancy follow-up	Follow-up 1 year
Information and counseling	*						
Signing of informed consent	*						
Treatment-related data collection	*				*	*	*
Randomisation	*						
Transvaginal ultrasound scan	*	*				*	
Blood sample	*	*	*	*	*		
Quality of life questionnaire						*	

*All participants.

### Objectives

At present, there is no clear evidence to suggest that LPS is required for NC-FET cycles following spontaneous ovulation. Therefore, there is still a fierce debate in clinical practice about whether patients treated with NC-FET should receive LPS. Our hypothesis is that no LPS is not inferior to OPRs in patients treated with LPS.

### Eligibility criteria

#### Inclusion criteria

Having regular ovulatory cycle; at least one embryo or blastocyst available for transfer.

#### Exclusion criteria

Age ≥ 45 years old, body mass index (BMI) ≥ 30 kg/m^2^; oocyte donation cycle; chromosomal abnormalities in both or one of the couples.; egg donation cycle; history of pelvic chemoradiotherapy; polycystic ovarian syndrome (PCOS); ovarian endometrioma, uterine fibroids, endometrial polyps or intrauterine adhesions requiring surgical treatment; history of repeated implantation failure (Infertile patients < 40 years old experience ≥ 3 oocyte retrieval cycles, and fresh or FETs cumulatively transfer at least four high-quality embryos without clinical pregnancy) and recurrent pregnancy loss (two or more pregnancy losses). Patients may withdraw from the study at any time without reason.

### Study population and recruitment

The study population include patients undergoing elective freeze-all strategy following IVF/ICSI cycles. Morphological evaluation of cleavage-stage embryos and blastocysts will be performed according to the Racowsky et al. **(19)** and the Gardner Scoring System **(20),** respectively. At least one grade I or II embryo with D3 blastomeres > 6 or high-quality blastocysts with a score ≥ 3BB will be cryopreserved. The investigators will contact all patients interested and eligible for the study by telephone. Patients interested in participating in the study will visit the corresponding reproductive center on days 2–4 of the menstrual cycle, after having fully understood the content of the study. Here, they further understand the details of the study and sign an informed consent. Each individual may be included only once and only in the first FET cycle after the oocyte retrieval. All medical personnel in the study will receive all necessary information and training to uniformly handle patients at each reproductive center. All sites staff have sufficient experience in conducting clinical trials.

### Randomization

Randomization will be performed by an independent statistician using a computer-generated randomization schedule with block randomization (block size of four) stratified by female age (< or ≥ 35 years) at LH-surge day in NC-FET cycle. Patients will be randomized in a 1:1 ratio to one of the following groups: (i) LPS group: Patients will receive vaginal combined intramuscular P_4_ treatment starting on the day of ovulation. (ii) Non-LPS group: Neither LPS nor any other therapies are administered to patients.

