### Non-inferiority design and power calculation

The present study will adopt the non-inferiority design. Due to previous studies showing that NC-FET treated with LPS does not achieve the same outcome as NC-FET treated without LPS, and that treatment without LPS has the advantages of being less costly and less painful. Specifically, we assumed a 10% margin of non-inferiority and a 50% OPR in two arms based on our center’s experience with FET. The number of cases in each group was calculated at 429, according to the design of 1:1 parallel non-inferiority, the unilateral test with alpha = 0.05, and the power of 90%. Assuming a drop rate of 15%, there are 505 cases per group and 1,010 cases for the two groups.

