## Trial status

The trial was registered on 14 March 2022 (ChiTR). The actual study start date was 1 July 2022 and the expected study end date was 31 December 2023. The enrollment start date was 15 July 2022; the anticipated enrollment end date was 31 May 2023.

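### A single block size of four, published during enrolment of an open-label trial, lets anyone who can follow an age stratum's sequence know a third of allocations in advance

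*Protocol article*

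**What the plan says.** The Randomization section of the protocol article describes a "computer-generated randomization schedule with block randomization (block size of four) stratified by female age". The only stratum named is age: "stratified by female age (< or ≥ 35 years) at LH-surge day in NC-FET cycle". The ratio is 1:1, and the person responsible is named: "Randomization will be performed by an independent statistician".

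Under Study design the trial is an "open-label, non-inferiority RCT, including reproductive centers of four tertiary care hospitals in mainland China". The Highlights add: "Physicians and participants could not be blinded to treatment allocation".

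The article carries the publication date 15 November 2022. Trial status gives the recruitment dates: "The enrollment start date was 15 July 2022; the anticipated enrollment end date was 31 May 2023". The block size therefore became public about four months into a planned enrolment of about ten and a half months.

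The article does not say whether one pair of age lists serves all four centres, how each allocation is released, or whether the block size was withheld from sites.

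**The concern.** Permuted blocks of one known size can be decoded when past allocations are visible. After two allocations to the same arm at the start of a block of four, the next two are known. The fourth allocation in any block is always known. Masking would normally hide past allocations, but here there is none.

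Staff who can predict the next arm can, knowingly or not, bring a woman forward or hold her back according to her prognosis. An intention-to-treat analysis does not remove bias that enters before allocation. In a non-inferiority trial such bias can work in either direction: it can hide a real disadvantage of omitting luteal support or create an apparent one. The question is how predictable the sequence really is, and how much of the margin that could use up.

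**Working it through.** **Inputs from the protocol article.** Block size 4, ratio 1:1, two age strata (Randomization); four centres (Study design); no blinding (Highlights). From Non-inferiority design and power calculation: "we assumed a 10% margin of non-inferiority and a 50% OPR in two arms", one-sided alpha 0.05, power 90%, dropout 15%.

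**The plan's own figure.** The article gives no figure on predictability. Its sample size reproduces: (1.645 + 1.282)² × (0.25 + 0.25) / 0.10² = 428.2, so 429 per group; 429 / 0.85 = 504.7, so 505 per group. The point below does not change it.

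**Case A: the full sequence in a stratum is visible.** There are six equally likely arrangements of two and two. The guesser always names the arm that is behind.

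| Position in block | Chance of a correct guess | Known for certain |
|---|---|---|
| 1 | 1/2 | never |
| 2 | 2/3 | never |
| 3 | 1/3 × 1 + 2/3 × 1/2 = 2/3 | in 1/3 of blocks |
| 4 | 1 | always |

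Correct guesses: (0.500 + 0.667 + 0.667 + 1) / 4 = 2.833 / 4 = 70.8%. Known for certain: (1/3 + 1) / 4 = 33.3%.

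**Case B: two age lists shared by four centres, each centre seeing only its own patients.** This structure is an assumption. Simulation of a list of 505 with fixed blocks of four, patients arriving at the centre at random:

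- Centre with a quarter of recruitment: about 51% correct by following its own tally, and about 55% to 56% by better rules such as guessing the opposite of the last allocation.
- Centre with half of recruitment: up to about 59%.
- No allocation is known for certain in either situation.

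**Translation into bias.** Assume that staff enter women whose expected ongoing pregnancy rate is v points above average when they guess one arm and v points below when they guess the other. With a proportion p of guesses correct, each arm's mean shifts by v(2p − 1) in opposite directions, so the bias in the difference is 2v(2p − 1). The values of v are illustrative; the documents give none.

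| v (points) | Case A, p = 0.708 | Case B, p = 0.55 |
|---|---|---|
| 1 | 0.8 | 0.2 |
| 2 | 1.7 | 0.4 |
| 5 | 4.2 | 1.0 |

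A bias equal to the whole 10-point margin would need v = 10 / (2 × 0.417) = 12 in case A, and v = 10 / (2 × 0.10) = 50 in case B.

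**Effect of varying the block size.** With sizes drawn at random from 4, 6 and 8 and the whole list visible, tally guessing is right about 68% of the time, against 71% with fixed fours. The larger change is in certainty: without knowing where a block ends, the guesser loses most of the allocations that were known in advance.

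**The case against.** The strongest reply is that the exposure is probably near the bottom of the range. Age is the only stratum named, so the natural reading is two lists common to all centres, which hides most of the sequence from any one of them. An independent statistician performs the randomisation, and the full protocol may describe concealed central release; its absence from an article is not an error. All of this stands, and it limits the size of the problem. It does not dispose of it: concealing the list does not prevent deduction from unmasked past allocations, and nothing in the article shows that staff at different centres cannot pool what they see.

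A reader might infer that leaving centre out of the stratification is part of what makes allocations guessable. The reverse is true. A shared list lowers predictability at a site to about 51% to 56% at a quarter of recruitment. Adding centre to age (eight strata) would show each site its own full sequence and raise tally guessing to about 68% even with blocks of 4, 6 and 8. Balance between arms within centres is a separate matter and a trade-off.

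A reader might also infer that selection could produce or hide a difference as large as the margin. The shifts of 12 and 50 points that this would need are not plausible; the second would require expected rates of 0% or 100% around the assumed 50%.

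Finally, the section can be read as placing randomisation on the day of the LH surge, after consent, which would leave less room to time entry. Table 1 puts it at the baseline visit, so this protection cannot be relied on.

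**Conclusion.** The point holds as a weakness in a stated rule that is cheap to improve. One block size, disclosed during enrolment of an unblinded trial, gives anyone who can follow a stratum's sequence certainty about 33% of allocations and a 71% success rate in guessing. With age lists shared by four centres and no exchange of information between them, success falls to about 51% to 56% at a quarter of recruitment and about 59% at half.

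The potential bias is part of the 10-point margin, not the whole of it: about 0.8 to 4.2 points in the worst case and 0.2 to 1.0 points with a shared list. These figures rest on an assumed selection of 1 to 5 points in expected ongoing pregnancy rate acted on at every entry, and on a list structure that the article does not state. The documents contain no evidence that allocations have actually been predicted or used in this way.

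**What to change.** For the participants still to be randomised, the independent statistician should regenerate the schedule, still stratified by age only, with block sizes varying at random (such as 4, 6 and 8). The sizes and their order should not be disclosed to sites or published before enrolment closes.

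The cost is a formal amendment through the committee described under Ethics and dissemination, and a slightly larger possible imbalance between arms at the end of each stratum. The sample size is unaffected. The gain should not be oversold: for someone who sees the whole list, tally guessing falls only from 71% to about 68%. What the change mainly buys is the loss of most of the certainty about upcoming allocations.

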### Interventions

Frozen-thawed embryo transfer will be performed in NC with spontaneous ovulation. Transvaginal ultrasonography (TVUS) is used to monitor follicular development and endometrial growth. In the late follicular phase, that is, on days 8–12 of the cycle (depending on the length of the patient’s menstrual cycle), when the dominant follicle develops to a mean diameter of more than 14 mm, serum LH level is monitored every other day until the LH surge appeared (21). When the endometrial thickness reaches more than 8 mm and the endometrium is classified as type A or B, embryo transfer is performed 4 days (D3 embryos) or 6 days (D5/D6 blastocysts) after the appearance of the LH surge. If luteinization of unruptured follicles occurs, embryo transfer is canceled. Plasma hCG levels were measured 14 days after embryo transfer.

Patients in the LPS group are given P_4_ sustained-release gel Crinone ^®^ 8% (Crinone, Merck Serono, Switzerland) vaginally, 90 mg/time, once a day and P_4_ injection (Zhejiang Xianju Pharmaceutical Co., Ltd., Zhejiang, China) intramuscularly, 20 mg/vial, twice a day until 14 days after FET (21). For pregnant women, LPS treatment should be continued until 10 weeks of gestation.

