### Drop-outs and cancel cycles

Dropout refers to the study participants’ voluntary decision to withdraw from the study due to personal subjective factors. The canceled cycles were those who were forced to cancel the cycles due to endometrial lesions found in TVUS, failure of follicular development or failure of embryo thawing and resuscitation up to 21 days in the cycle. The researchers will make a detailed summary of the number and causes of dropout and cancelation in both groups and completion characteristics within and between groups. Based on our experience, the dropout rate will be up to 15%. If the actual dropout rate is higher than expected, we will discuss the potential bias, analyze the differences between the results and draw conclusions accordingly.

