### Statistical analysis and interpretation of data

The intention-to-treat (ITT) analysis includes both dropout and cancelation cycles. The per-protocol (PP) analysis includes all patients who strictly followed the study protocol. In the as-treated analysis, patients who subsequently received LPS but not NC-FET are excluded, however, those who subsequently received LPS from NC-FET until 10 weeks of gestation are included. We measured OPRs and identified differences between groups based on relative risk (RR) and 95 confidence interval (CI). PP analyses will be also performed for all reproductive outcomes.

Continuous data were compared using Student’s *t*-test and results are presented as mean (standard deviation, SD) or median (inter-quartile range, IQR). Categorical data with expected frequencies less than five is assessed using χ^2^ analysis and Fisher’s exact test. *P*-values less than 0.05 is considered statistically significant. Data analysis will be performed using SPSS 26.0 and R 4.1.3. Multivariate logistic regression analysis will be performed to identify variables independently associated with OPR.

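### The protocol gives two conflicting randomisation times (LH-surge day and cycle days 2–4), so it is unclear whether cycles cancelled before treatment belong to the ITT set

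*Protocol article*

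**What the plan says.** Five places in the protocol article bear on when a woman is randomised and who is then analysed.

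- **Randomization:** the schedule is blocked and "stratified by female age (< or ≥ 35 years) at LH-surge day in NC-FET cycle". The LPS arm has "treatment starting on the day of ovulation", so the arms are managed alike until then.
- **Table 1 (Overview of study visits):** the only mark in the randomisation row is in the column headed "Baseline * (2–4 days at menstruation"). The next column, which runs from the late follicular phase to ovulation day and would contain the LH surge, has no mark in that row.
- **Drop-outs and cancel cycles:** cancelled cycles include those stopped for "failure of follicular development or failure of embryo thawing and resuscitation up to 21 days in the cycle". The investigators will summarise the "number and causes of dropout and cancelation in both groups".
- **Statistical analysis and interpretation of data:** "The intention-to-treat (ITT) analysis includes both dropout and cancelation cycles".
- **Interventions:** one cancellation rule acts after the surge: "If luteinization of unruptured follicles occurs, embryo transfer is canceled".

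The Abstract states that "the primary statistical strategies were intention-to-treat (ITT) and per-protocol (PP) analysis".

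**The concern.** The time of allocation decides who is in the trial, and the text and the visit table give different answers. The cancellation and ITT rules side with the table: a cycle with no developing follicle has no LH surge, so it can belong to an arm only if allocation came earlier.

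This matters more in a non-inferiority trial than in a superiority trial. Under baseline allocation, women whose cycle fails before ovulation never reach the point at which the arms differ. If they are counted as not pregnant, they add the same proportion of non-events to each arm. A true loss from omitting luteal support then looks smaller in ITT while the margin stays at 10 points. The Introduction itself says that natural-cycle transfer has high cancellation rates. The trial is also open-label, so under baseline allocation the arm could be known throughout the monitoring period in which a cycle may be cancelled.

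**Working it through.** **1. Reproduce the plan's sample size, to establish the scale of the margin.** Inputs from Non-inferiority design and power calculation: 50% in both arms, margin 10%, one-sided alpha 0.05, power 90%, dropout 15%.

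n per arm = (1.645 + 1.282)² × (0.5×0.5 + 0.5×0.5) / 0.10² = 428.2, rounded up to 429. Then 429 / (1 − 0.15) = 504.7, rounded up to 505. Both stated figures reproduce on a risk-difference basis, so the margin is 10 absolute percentage points.

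**2. Compare the two candidate times.**

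| Point | LH-surge day | Baseline, days 2–4 |
|---|---|---|
| Randomization section | fits | fits only if the surge-day phrase dates the stratifying age alone |
| Table 1 | does not fit | fits |
| Failed follicular development counted by arm and kept in ITT | does not fit | fits |
| Unruptured follicle or thaw failure in ITT | possible | possible |

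**3. Illustrate the dilution.** Let c be the share of each arm cancelled before treatment and counted as not pregnant. The protocol gives no value for c, so 5% to 15% is an assumption. Take the true rates among transferred women exactly at the margin: 50% with support and 40% without. Use 505 per arm.

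- ITT rates: 0.50(1 − c) and 0.40(1 − c)
- ITT difference: 10(1 − c) points
- SE = √{[p₀(1 − p₀) + p₁(1 − p₁)] / 505}
- Chance of declaring non-inferiority = Φ[(0.10 − difference)/SE − 1.645]

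At c = 15%, p₀ = 0.425, p₁ = 0.340, the difference is 0.085 and SE = √[(0.2444 + 0.2244)/505] = 0.0305. So Φ(0.015/0.0305 − 1.645) = Φ(−1.15) = 12.5%.

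| c | ITT difference (points) | False non-inferiority, one-sided 0.05 | With a two-sided 95% CI |
|---|---|---|---|
| 0 | 10.0 | 5.0% | 2.5% |
| 5% | 9.5 | 6.9% | 3.6% |
| 10% | 9.0 | 9.3% | 5.1% |
| 15% | 8.5 | 12.5% | 7.1% |

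A simulation of 400,000 trials at c = 15% gave 12.6% and 7.2%.

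**4. Check the other scale and the other analysis set.**

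- Relative risk: 0.40(1 − c) / 0.50(1 − c) = 0.80 for every c. Against an assumed relative-risk margin of 0.80, the error stays at 5.0%.
- Per protocol at c = 15%: 505 × 0.85 ≈ 429 per arm, rates 50% and 40%, error 5.0%. Power under equal 50% rates is 90.1%.

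**The case against.** **The surge-day phrase may date only the age.** It directly follows the age cut-off and could fix only the age used for stratification. The other passages would then agree on baseline. This reading is possible, so the conflict should not be put more flatly than that. It does not remove the need for correction: the Randomization section would then give no time of randomisation and would stratify on age at a day not yet reached.

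**The rise from 5.0% to 12.5% is not all due to timing.** This stands. Unruptured follicles, thaw failure and voluntary dropout can all follow the surge and stay in ITT under either time, so randomising on LH-surge day would not bring c to zero. If, purely for illustration, 10 of 15 points would occur anyway, timing would account for a rise from 9.3% to 12.5%. Nor is the protocol's 15% a cancellation rate: it is an allowance for dropout, which the protocol defines as voluntary withdrawal.

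**The planned effect measure is a relative risk, and PP is also primary.** Both points stand as limits. Equal cancellation does not dilute a relative risk, and PP largely removes untreated cancelled cycles. However, the only margin stated is absolute, and nothing says that ITT and PP must agree before non-inferiority is declared.

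**Some harms are conjecture.** A reader might infer that centres are already randomising at different times. No passage shows this, and Study population and recruitment describes training for uniform handling. Arm-aware cancellation is likewise only a possibility, and some scope for it would remain after the surge.

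**Conclusion.** The inconsistency is real and unreconciled: the protocol does not settle when allocation occurs, and its cancellation and ITT rules fit only allocation before the surge. If allocation is at baseline, ITT judged on the absolute 10-point margin is diluted towards non-inferiority. The direction is clear for cancellations that are equal in both arms and counted as not pregnant. The size is not known. The figures of 6.9%, 9.3% and 12.5% (for 5%, 10% and 15% of each arm) rest on assumed cancellation shares and on true rates placed exactly at the margin.

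A reader might infer that the trial has a 12.5% chance of a false conclusion. The documents do not support this. That figure belongs to one of two primary analysis sets, on one scale, at an assumed rate, and only its pre-surge part is due to timing. This should be fixed, but it does not by itself invalidate the design.

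**What to change.** 1. State which randomisation time has actually been used at each of the four centres.
2. By formal amendment, set one time in the Randomization section, Table 1, Drop-outs and cancel cycles, and the statistical analysis section. LH-surge day is preferable because it lies close to the point at which the arms diverge. If it is adopted, move the Table 1 mark to the late-follicular/ovulation column.
3. From that amendment on, count cycles that fail before randomisation as not randomised.
4. Keep every woman already randomised in ITT and record her actual randomisation time. Enrolment began on 15 July 2022, before the article appeared, so women already allocated cannot be relabelled as screen failures.
5. Report pre-treatment cancellations by arm, and require non-inferiority in both ITT and PP.

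Cost: a site memo is not enough, because Ethics and dissemination requires formal amendment by a committee for changes affecting design or conduct. If centres have been randomising at baseline, the trial will contain two randomisation times, which must be reported. The allocation step itself moves only a few days, within existing monitoring visits.
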